### Recruitment process

Participants will be recruited from acute mental health inpatient wards for adults. Methods used to recruit will include discussing the study with inpatient staff teams, individually and at ward meetings, and inviting them to introduce the study to potentially eligible participants, screening of caseloads by Trust staff with access to case notes, and distribution of advertising materials onwards and via local social media. Inpatient staff will be asked to consider the stage of service users’ recovery and likely capacity to understand the study purpose and requirements before approaching patients on our behalf. Posters will also be put up, and flyers distributed on recruiting wards to advertise the study, and the study discussed at community meetings for patients when there are opportunities. We will also promote the study on social media related to the trust and share advertising material with relevant local advocacy and voluntary services within the trust’s locality.

Participants who are willing to consider participating in the study and are deemed likely to be eligible by ward staff will be approached either by a research worker within the study team or by a Clinical Studies Officer (these are members of NHS Trust Research and Development teams who are embedded with inpatient teams for the purpose of identifying and recruiting study participants). Patients can also self-refer by contacting the research team directly via details on recruitment materials. Potential participants will be provided with a verbal overview of the study and given a copy of the participant information sheet. They will be given at least 24 h to consider whether they are interested in the study. If they remain interested in taking part after this, their capacity to give informed consent will be assessed (including the understanding of trial processes and the intervention), and participation will begin once written informed consent has been obtained by a researcher.

### Interventions

The *intervention group* will be offered the co-designed study intervention as described above, consisting of four initial sessions delivered approximately once a week, and subsequent monthly contacts up to a year post-randomisation. This support will be in addition to treatment as usual (TAU), during hospital admission and post-discharge.

The *control group* will be offered TAU, which is a standard practice for feasibility trials. This potentially includes multi-disciplinary care from staff including mental health nurses, nursing assistants, psychiatrists, pharmacists, occupational therapists, and psychologists in both the inpatient and community settings. TAU will also be offered to the intervention group.

### Allocation

Randomisation will take place following the completion of baseline measures. Researchers at UCL who are independent of the study will allocate participants via a computer-generated allocation sequence to either the intervention or control group in a 1:1 ratio using block randomisation stratified by site (3:3:2 ratio inner London: outer London: North-West England) and ethnicity (ethnic minority groups at higher risk of detention vs lower risk groups 1: 1 ratio).

Some of the study team will be unblinded so that they are able to deal with any issues with intervention delivery as they arise. Other members of the study team, such as the study research assistants who will be collecting follow-up outcomes, will be kept blind to treatment allocation as far as possible. The study team will liaise with the PMHWs, who will not be blinded, to minimise the likelihood that the blind researchers will be accidentally exposed to information about group allocation (known as ‘blind breaks’). Blinding will be monitored, and if any blind breaks occur, they will be systematically recorded.

### Sample size

We aim to recruit 80 participants in line with recommendations by Consolidated Standards of Reporting Trials (CONSORT) for a pilot randomised controlled trials (RCTs) and to randomised them to either intervention or control group [28]. This is deemed a sufficient sample to examine the primary aim of the study, which is assessing feasibility parameters to inform decisions about a future fully-powered confirmatory trial—we have considered the need to have sufficient data both about the sample as a whole and high-risk ethnic groups.

The statistical power of the current feasibility trial will result in 80% power (with a two-sided alpha of 5%) of detecting a reduction in rates of compulsory readmission from 50 to 20% following the recruitment of 80 participants. Such a large difference between arms is not expected, but the risk of detention in each group will inform the calculation of sample size and can also inform a calculation of how likely it is that a significant result would be achieved in a full study (see Analysis section below).

### Discontinuation/withdrawal of participants

When consenting to participate in the trial, participants are consenting to randomisation, assessments, intervention, follow-up, and data collection. Participants also consent to the research team continuing to collect data from medical records should they lose capacity at any point during the trial, unless this consent is withdrawn. A participant who is known to lack capacity at the time of a follow-up interview will not be contacted for further assessments, but data collected up to that point will be retained, and the team will continue to use data from the participant’s medical records unless a request to withdraw from the use of this data is received, in which case no further data will be collected. If a participant who has lost capacity regains it within the timeframe for interview assessments, they will be contacted to seek consent to carry these assessments out (this maximises the numbers who can be included despite the transient loss of capacity which is frequent among people with severe mental health problems).

### Outcomes

The primary goal will be to assess feasibility outcomes. We will also collect data on planned outcomes for a future randomised controlled trial of the intervention, allowing assessment of the feasibility of intervention delivery and trial processes, collection of data needed to inform a power calculation for a definitive trial, and a preliminary assessment of the likelihood of a positive result from a definitive trial.

### Feasibility outcomes

Detailed trial parameters will be recorded. These will include rates and routes of identification of potentially eligible participants at each site, recruitment and acceptance of randomisation, rates, and patterns of attrition from treatment and trial assessments, delivery of each intervention component, completion rates for individual outcome measures, rates of serious adverse events in each arm of the trial, and event rates for the planned primary trial outcome of compulsory readmission.

## Progression criteria

The trial parameters will be assessed against the following progression criteria:Recruitment within 9 months of 80 trial participants.At least 50% of these participants are from ethnic backgrounds associated with an elevated risk of being compulsorily admitted.At least 85% data completeness on primary outcome measure for trial (repeat compulsory admission within a year)At least 60% data completeness for secondary outcomes at 1 yearAt least 75% of intervention participants have developed a crisis plan and have received at least 3 intervention sessions.

If the above are achieved, we will assume that current protocols and procedures are suitable for a full trial, testing the hypothesis that the intervention reduces compulsory hospitalisation. If we fall short on any criteria by up to 20% we will consider whether improvements can be made in procedures and processes to make a full trial achievable. If we fall short by more than 20%, we will assume that a full trial is only justified if substantial changes are made and a further pilot takes place.

### Trial outcomes

Trial outcomes will be measured via clinical records and interviews with study researchers. Research interviews will be conducted at baseline prior to randomisation, and at 6 and 12 months after randomisation. A final follow-up point at 24 months will involve health record data only.Primary trial outcome

The planned primary outcome for a future definitive trial is whether the participant has been compulsorily detained in a hospital under Sect. "Secondary outcomes" or Sect. 3 of the Mental Health Act within 1 year of randomisation. This data will be extracted from participants’ health records.2.Secondary outcomes

From health records:

The following will be obtained from electronic data about patients held by Trusts:Compulsory admission within 24 months of randomisation.Whether participants remain engaged with services

### From research interviews

The remaining secondary outcome measures will be collected by a research assistant blind to treatment allocation. The following measures will be administered during a face-to-face, video, or phone interview (depending on service user preference, with face-to-face or video call preferred if possible):Satisfaction with services will be examined using the Client Satisfaction Questionnaire (CSQ) [29]. This is an 8-item scale where participants can rate their satisfaction with various aspects of their care on a 4-point Likert scale.Self-rated recovery will be measured by the 15-item Questionnaire about the Process of Recovery (QPR) [30]. Participants can score from 0 (disagree strongly) to 4 (agree strongly) on each item and score up to a maximum of 40 on the scale.Self-management confidence will be measured using the Mental Health confidence scale [31]. Participants report their confidence in managing their mental health for 16 items rated on a Likert scale from very non-confident to very confident.Quality of life will be measured by the REQOL-10 [32] and EQ-5D-5L [33]. They are both widely used measures in clinical trials with populations with severe mental health problems. On the REQOL, participants rate their quality of life on 10 items from 0 to 4. A participant can score a total of 40 and this information can be used to derive disability-adjusted life years (QALYs). For the EQ-5D-5L, we used only the physical health item, where participants can score from 1 (no problems) to 5 (severe problems). This information can be used to derive quality-adjusted life years (QALYs)Psychiatric symptoms will be assessed using the Brief Psychiatric Rating Scale (BPRS) [34]. Participants are rated by a researcher/research assistant on 18 items from 0/ NA (not assessed) to 7 (extremely severe) to give an overall score of psychiatric symptoms.

### Health economic analysis

Service use data will be collected using an adapted version of the Client Service Receipt Inventory (CSRI) [35]. Costs will be calculated by combining this information with appropriate unit costs. The costs of the intervention will be calculated from information on staff time and other requirements.

Descriptive data such as demographic and clinical/service user characteristics will also be recorded, including Community Treatment Order status, previous admission and compulsory detention history clinical diagnosis, and demographic data including age, sex, and ethnic group.

### Qualitative study

An embedded qualitative study, involving semi-structured interviews with participants in the experimental group and with the PMHWs delivering the intervention, will be used to investigate experiences and acceptability of the intervention and desirable modifications before proceeding to a full trial.

Semi-structured interviews will be conducted with up to 30 consenting intervention group participants: the size of the sample will be determined by when we appear to have attained thematic sufficiency and a sample that is representative in terms of demographics and diagnosis (or else may reflect the number of intervention group participants who are willing and able to give informed consent to an interview).

Interviews will be carried out between 6 and 9 months after recruitment, usually by service user researcher members of the co-production group to facilitate empathy and open disclosure, supported by the research team, or if not available, interviews will be carried out by a study research worker. Study researchers will interview the PMHWs who have delivered the intervention.

Topic guides will explore experiences of the intervention and its acceptability, barriers, and facilitators to making use of it, possible mechanisms of effect, potential benefits or harms, and suggested changes. Data collection and analysis will be guided by the Theoretical Framework of Acceptability [36] using thematic analysis, exploring in relation to the intervention the seven domains of acceptability specified in this framework: affective attitude, burden, perceived effectiveness, ethicality, intervention coherence, opportunity costs, and self-efficacy.

### Participant timeline

Intervention development took place between May 2021 and March 2022. The six preliminary patients were recruited in April and May 2022. For the feasibility study, baseline recruitment will be from May 2022 to the end of January 2023 with an estimated 10 participants recruited per month. Participants will be followed up 6 months and 12 months post-baseline to complete all measures again, and medical records will be assessed 24 months post-baseline.

Please see Table 1 (SPIRIT Table) which outlines the schedule of enrolment, interventions, and assessments.

**Table 1 Tab1:** SPIRIT Table—schedule of enrolment, interventions and assessments

	Screening (pre-treatment assessment)	Intervention phase	6-month post-baseline (post-therapy)	12-month post-baseline (follow-up)	24-month post-baseline (follow-up)
	Day 1–7	Week 1–52	Week 24	Week 52	Week 104
Informed consent	X				
Eligibility confirmation	X				
Randomisation	X				
Compulsory admission				X	X
CSQ	X		X	X	
QPR	X		X	X	
REQOL	X		X	X	
MHCS	X		X	X	
CSRI	X		X	X	
Intervention delivery		X			
Qualitative interview (intervention arm participants only)			X^a^		

^a^Will be conducted 6–9 months post-randomisation

## Data management, security and analysis

### Data management and security

All staff have been trained in and will adhere to the requirements of the General Data Protection Regulation (GDPR) (2016/679) and the UK Data Protection Act (2018) with regard to the collection, storage, processing, and disclosure of personal information, and will uphold the Act’s core principles.

Identifiable information (name, address, contact details, and GP name) will be stored securely and separately from other study data on a password-protected database. The Case Report Forms (CRFs) will not bear the participant’s name or other personally identifiable data. Data on service use, psychiatric diagnosis, and related symptoms, risk assessment, and hospitalisation will be extracted from Trusts’ electronic records. All information extracted from medical notes will be directly added to the CRF and anonymised through the use of a participant number.

All electronic data collected during the study will be stored on a password-protected REDCAP database, which is a secure web application for building and managing online databases. The database is password protected and only the trial manager and researchers recruiting and enrolling participants in the study have access.

Participants are made aware at the time of recruitment that if a participant discloses a serious risk of harm to themselves or others, researchers would consider breaching participants’ confidentiality to share the necessary information with the relevant clinical team or, if the urgency of the situation did not allow prior discussion with clinical services, the emergency services. However, this would be judged on a case-by-case basis, and confidentiality would only be breached for serious disclosures where there is considerable concern about immediate risk to self or others.

## Data analysis

### Statistical analysis

A separate Statistical Analysis Plan will be pre-specified which will be held within the Statistics Master File. It will contain following sections: (I) Introduction, (ii) study methods, (iii) statistical principles, (iv) trial population, (v) analysis of primary and secondary outcomes). We will register this SAP in a public-facing database (e.g. clinicaltrials.gov) prior to unblinding of the statistician and the commencement of data analysis. The current trial statistician (RG) and oversight statistician (NF) remain blinded to intervention allocation during the conduct of the trial and shall remain so until after the end of data collection.

### Feasibility outcomes

The primary aim of the study is to assess the feasibility of recruiting, randomising, and retaining 80 participants in the trial. Descriptive statistics will include the rates of identification of potentially eligible participants, recruitment and acceptance of randomisation, rates, and patterns of attrition from treatment and trial assessments, delivery of each intervention component, completion rates for individual outcome measures, and event rates on the outcome of compulsory readmission.

### Trial outcomes

The analysis population will consist of all eligible patients who have given consent and have been randomised to an intervention arm irrespective of the completion of the study. We will use an intention-to-treat analysis.

For binary and continuous trial outcome variables, we will assess characteristics of the statistical distribution, enabling us to power a larger subsequent RCT.

### Sub-group analyses

Subgroup analyses are not envisaged especially given the relatively restricted sample size and the resultant lack of power for multiple analyses.

### Inferential analyses

This pilot study will not have sufficient statistical power to assess the effectiveness of the intervention but will allow an assessment of whether the direction and magnitude of any effect found for the proposed primary outcome are consistent with a hypothesis that the programme is effective in reducing repeat detentions. For this reason and to test the analysis envisaged for a future, fully powered, effective RCT, primary outcome at follow will be compared between study arms, using appropriate multi-level models. Our planned analysis is hierarchical multi-level modelling, allowing for the clustering of residuals between centres by introducing the variable coding for centre as a random intercept. We will enter all other stratification variables as fixed effects. Other potential baseline covariates (e.g. age, ethnicity) will be entered in serial adjusted models where relative fit will be assessed using Akaike and Bayesian Information Criteria. The goodness of fit will be determined using Hosmer Lemeshow test of fit. We will assess the robustness of the results to missing data by carrying out sensitivity analyses in which the missing data are assigned extreme values to determine the effect of potential extreme missing values on the stability of the reported results. We will assess the effect of time by analysing results with time as a random slope variable.

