### Intervention content and delivery

The intervention drafted through the above process consists of four initial sessions with a PMHW, followed by monthly check-in sessions for the remainder of a year. PMHWs are clinical psychologists or other qualified mental health professionals with experience in delivering structured interventions to people with significant mental health problems. PMHWs aim to complete as many of these initial sessions, each lasting up to an hour, as possible while participants are still inpatients, but continue the intervention in the community following discharge when needed.

The key activities which PMHWs aim to complete in the first four sessions with each intervention participant are the following:Development of a collaborative formulation to allow an understanding of the pathway by which the participant came to be compulsorily detainedCreation of a personalised crisis plan, addressing early warning signs of a crisis and ways of responding, potentially including family, friends, and professionals from whom they feel they may be able to get support. This is in digital and/or paper form, according to preference. This includes an opportunity to develop a “Message to future self” in written or recorded form, which may include advice on how to manage an incipient crisis or remind them of important aspirations.Development of an advanced statement recording care and treatment preferences if they become unwell in the future.Exploration of aspirations and recovery goals for the future.

As engagement is a central aim, there is considerable flexibility in the order of delivery of these activities, and in whether some of them continue into the 11 monthly check-in sessions. These check-in sessions are initiated by the PMHW and are intended to involve providing support, continuing, or revisiting elements of the intervention, checking for identified early warning signs, and prompting responses to avert a crisis. These sessions are up to 45-min in duration. The main modes of delivery are face-to-face for the initial sessions and phone or video calls for subsequent check-ins, but with flexibility to accommodate individual preferences and circumstances: text and WhatsApp messaging are also used to maintain contact.

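### The planned primary model, a rehearsal for the definitive trial, allows for clustering by centre but not by the PMHWs who treat the intervention arm only, and no such allowance is stated for the definitive sample size

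*Protocol article*

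**What the plan says.** All places are in the protocol article.

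- **Allocation:** individuals are randomised to "intervention or control group in a 1:1 ratio using block randomisation stratified by site" and by ethnicity (higher-risk v lower-risk groups).
- **Intervention content and delivery:** the intervention is "four initial sessions with a PMHW, followed by monthly check-in sessions for the remainder of a year". **Interventions** repeats this as "subsequent monthly contacts up to a year post-randomisation". Controls receive usual care and have no PMHW.
- **Inferential analyses:** the primary outcome is compared between arms in a multi-level model, "allowing for the clustering of residuals between centres by introducing the variable coding for centre as a random intercept", with the other stratification variables as fixed effects. One stated reason for running it is "to test the analysis envisaged for a future, fully powered, effective RCT".
- **Sample size:** 80% power at a two-sided 5% level is given for a "reduction in rates of compulsory readmission from 50 to 20% following the recruitment of 80 participants". For the definitive trial, "the risk of detention in each group will inform the calculation of sample size". **Trial outcomes**, under Data analysis, adds that the distributions of the outcome variables will be examined for the same purpose.

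The article mentions no PMHW-level clustering, ICC or caseload, and does not give the number of PMHWs.

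**The concern.** This is an individually randomised trial with nesting in one arm: intervention participants are grouped by PMHW and controls are not grouped. The contact lasts as long as the primary outcome window, engagement is described as central, and delivery is deliberately flexible. The protocol therefore gives some reason to expect results to vary by worker.

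A centre intercept common to both arms largely cancels from the arm contrast. Variation between PMHWs exists in the intervention arm only and acts like an arm-by-centre difference. The common intercept does not remove it, even with exactly one PMHW per centre.

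Two distinct harms follow, depending on what is done later:

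- If the definitive trial keeps this model, its standard error is too small and the type I error exceeds 5%.
- If the definitive trial allows for PMHWs but was sized without them, it loses power.

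The model is presented as the rehearsal for the definitive trial, so an incomplete clustering structure would be carried forward.

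**Working it through.** **Inputs from the article.** 80 participants, 1:1, so 40 per arm; 50% v 20%; two-sided 5%. For a full trial, 43% v 28% is used as an illustration. It is the Zürich result quoted in the Background, measured over 2 years, whereas the planned primary outcome is at 1 year.

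**Assumed inputs.** 3 to 6 PMHWs in the pilot (mean caseload m = 40/3 = 13.3 to 40/6 = 6.7); caseloads of 13, 20 and 30 in a full trial; ICC 0.01 to 0.10; 90% power for the full trial (the article states no target for it).

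**Step 1: the article's own figure.** With a pooled variance under the null, 40 per arm gives 81.6% power, and 39 per arm (78 in total) reach 80%. With the unpooled variance:

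- SE = √[(0.50×0.50 + 0.20×0.80)/40] = √(0.41/40) = 0.1012
- 0.30/0.1012 = 2.963; power = Φ(2.963 − 1.960) = 84.2%

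The stated 80% reproduces as the figure for independent observations. The unpooled form is used below.

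**Step 2: clustering in the intervention arm only.** Variance = [pc(1−pc) + pt(1−pt)×DE]/n, with DE = 1 + (m−1)×ICC. For 3 PMHWs and ICC 0.05, DE = 1 + 12.33×0.05 = 1.617, SE = √[(0.25 + 0.16×1.617)/40] = 0.1128, and power = Φ(2.660 − 1.960) = 75.8%.

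| ICC | Pilot power, 3 PMHWs | Pilot power, 6 PMHWs |
|---|---|---|
| 0 | 84.2% | 84.2% |
| 0.01 | 82.5% | 83.4% |
| 0.05 | 75.8% | 80.3% |
| 0.10 | 68.2% | 76.5% |

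These are powers of a test that allows for the clustering. For a test that ignores it, a beta-binomial simulation of the two-proportion comparison (40,000 runs per setting, 3 PMHWs, common risk 35% or 50%) gave a type I error of 4.7-5.7% at ICC 0, 5.7-6.6% at ICC 0.01 and 8.5-9.6% at ICC 0.05.

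**Step 3: illustrative full trial.** n = (1.960 + 1.282)² × (0.2451 + 0.2016)/0.15² = 208.6, so 209 per arm.

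- *Clustering ignored.* Under the null with equal risks, the true SE divided by the model SE is √[(1 + DE)/2], so type I error = 2×[1 − Φ(1.960/ratio)]. For m = 20 and ICC 0.05: DE = 1.95, ratio = √1.475 = 1.214, type I error 10.7%.
- *Clustering allowed for, size unchanged.* Power uses the Step 2 variance with n = 209.
- *Size needed.* 208.6 × (0.2451 + 0.2016×DE)/0.4467. For m = 20 and ICC 0.05: 208.6 × 1.4287 = 298.

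| Caseload m | ICC | DE | Type I error if ignored | Power at 209 per arm if allowed for | Needed per arm (about) |
|---|---|---|---|---|---|
| 13 | 0.01 | 1.12 | 5.7% | 88% | 220 |
| 20 | 0.01 | 1.19 | 6.1% | 88% | 227 |
| 30 | 0.01 | 1.29 | 6.7% | 86% | 236 |
| 13 | 0.05 | 1.60 | 8.6% | 82% | 265 |
| 20 | 0.05 | 1.95 | 10.7% | 77% | 298 |
| 30 | 0.05 | 2.45 | 13.6% | 71% | 345 |

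**Cross-check on another base.** With the pooled formula, 80% power and m = 15, 159 per arm (318 in total) are needed without clustering. That size has 77.4% power at ICC 0.01 and 67.6% at ICC 0.05; 340 and 426 in total would be needed.

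**The case against.** **The ICC may be very small.** Detention is decided by two doctors and an Approved Mental Health Professional and is read from health records. The PMHW neither makes nor rates it, and PMHWs are trained, supervised monthly and logged for fidelity. This stands: the documents give no ICC, 0.05 is only an assumption, and at 0.01 the effect is modest. At ICC 0 nothing changes. A reader might infer that the pilot's intervals are too narrow as a matter of fact; the documents support this only conditionally.

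**The article does not say the definitive trial will be sized on arm risks alone.** This also stands. Those risks are to inform the calculation, which does not exclude a design effect. No definitive sample size exists yet, so none can be called underpowered. What can be said is that no PMHW allowance is stated.

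**The two harms should not be added together.** Correct. The 71-82% power applies to an analysis that allows for PMHWs. Under the model as written, power at ICC 0.05 would be about 84-87%, with an inflated type I error.

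**This is a feasibility trial, and the detail belongs in the SAP.** No progression criterion uses the effect estimate, the article disclaims power for effectiveness, and the pilot cannot estimate a PMHW variance well; with one PMHW per centre it is inseparable from a centre-by-arm effect. These facts limit the consequence for the pilot's own conclusions. They do not remove the point. The article states its clustering structure outright instead of leaving it to the SAP, and gives the model the job of testing the definitive analysis.

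**Conclusion.** The point holds in conditional form. The stated model omits the one level of clustering that exists in a single arm, and the centre intercept does not stand in for it. If outcomes vary between PMHWs, the standard error of the arm effect is too small.

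The size depends on inputs that the documents do not give. In the pilot, with 3 to 6 PMHWs, the power of a valid test falls from 84% by under 2 points at ICC 0.01, and to 76-80% at ICC 0.05. In the illustrative full trial the consequence is slight at ICC 0.01 and material at 0.05, and it grows with caseload. The full-trial figures also rest on a two-year result and an assumed 90% power target, so they show scale and are not a forecast.

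A reader might also infer that the 80% power in the Sample size section is an error. It is not: it reproduces, on the assumption of independent observations. The point should be corrected before the model is carried forward, but it does not threaten the feasibility objectives.

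**What to change.** 1. **Inferential analyses.** Keep the centre and ethnicity terms. State that the analysis envisaged for the definitive trial is partially nested, with a PMHW random effect in the intervention arm only. In the pilot, do not rely on estimating that variance. Instead report, as a sensitivity analysis, the primary-outcome effect with its confidence interval recalculated at fixed ICCs of 0, 0.01, 0.05 and 0.10, using the actual PMHW caseloads.
2. **Sample size, and Trial outcomes under Data analysis.** State that the definitive sample size will inflate the intervention-arm variance by 1 + (m − 1)×ICC over the same ICC range, with m the planned PMHW caseload.
3. **Optional.** Note beside the 80% power that it assumes independent observations.

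The cost is wording and one extra table. PMHWs already log their sessions, so the only data needed are which PMHW treated whom. The downside is somewhat wider intervals in the sensitivity analysis and a larger projected full trial.
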